### Sample size, power and effect size

The estimated sample size for randomisation is based on the CEQUEL study [32] that included similar participants in a depressive episode of BD from the UK NHS, and who had weekly remote monitoring of mood over a 52 week period. Dropout rates in this study were 20% at 12 weeks and 50% at 52 weeks. A power calculation demonstrates that 290 participants provides a 90% power of detecting a 3-point difference in QIDS-SR [33] between pramipexole and placebo (*p* < 0.05), based on a two-sample t-test at 12 weeks with a QIDS-SR [33] standard deviation of 7 and assuming a 20% dropout rate as seen in the CEQUEL study [32]. This sample size also provides approximately 80% power of detecting a 3.3 point difference in QIDS-SR scores [33] between the treatment arms at week 48 assuming the 50% dropout rate seen in CEQUEL [32] and the standard deviation used above. In a study of a similar population, a drop-out rate of 30% was experienced during the pre-randomisation phase [46]. As a result, it is anticipated that PAX-BD will need to recruit approximately 414 participants into the pre-randomisation phase trial to achieve the target of 290 participants randomised.

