#### Randomisation and blinding

Sealed Envelope, a secure web-based system managed centrally is used to randomise participants with concealed allocation. The first 10 participants are allocated randomly. Subsequently, a non-deterministic minimisation algorithm is used with an 80% bias in favour of allocations that minimise an imbalance on variables hypothesised to be related to prognosis at baseline: bipolar I or bipolar II based on DSM-5 criteria; severity of depression at randomisation (moderate, severe or very severe); age (18–50 or > 50); biological sex (male or female); UK site region (North, Midlands and East, London, South East, South West, Scotland, Wales or Northern Ireland); concurrent mood stabiliser (lithium, valproate, lamotrigine, carbamazepine or multiple mood stabilisers); concurrent antidepressant (yes or no); on an antipsychotic at randomisation (yes or no); number of mood episodes in the past year (< 4 or ≥ 4).

Pramipexole and matching placebo are manufactured by Wasdell then packaged and labelled by Modepharma. Trial medication is then delivered blinded to the CNTW pharmacy for storage and dispensing. The TMG is blind to treatment allocations. An unblinded Data Manager will provide the DMC the key to unblind treatment arms for closed reports. To prepare these reports, a trial statistician is partially blinded and provided data by the unblinded Data Manager where treatment arms are coded as A and B. Participants and staff at recruitment sites remain blinded for the duration of the study, though unblinding can occur in the event of a clinical emergency.

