### Statistical analysis

Full details of all statistical analyses will be specified in a pre-defined Statistical Analysis Plan. Initial descriptive analysis will present the profile of the participants and investigate differences in demographic and outcome measures between the two treatment arms at baseline. If significant differences are found, the variable may be added to the models testing the relevant study hypothesis. A two-sided significance level of *p* < 0.05 will be used throughout.

Analysis of the primary outcome measure of QIDS-SR [33] at week 12 will use Analysis of Covariance (ANCOVA) to examine the difference between the treatment arms with adjustment for baseline covariates including initial QIDS-SR score, other minimisation factors and anxiety (GAD-7) score [35]. Other baseline covariates will be examined for potential inclusion during the modelling process.

Weekly repeated measures scores for QIDS-SR [33] will be examined to ascertain participant compliance in completion. Should this be judged sufficient, a mixed effects linear regression model will be used to account for the repeated measures over time in comparing this outcome between the treatment groups. Other secondary outcome measures include: the proportion of participants in remission at 12 and 48 weeks (QIDS-SR score ≤ 5), the proportion of participants who have achieved a response at 12 and 48 weeks (QIDS-SR score reduction of ≥50% from baseline), proportion of time over 48 weeks that participants are free of depressive symptoms (QIDS-SR score ≤ 5), proportion of time over 48 weeks that participants are free of manic symptoms (ASRM score ≤ 5) and changes in psychosocial function determined by the WSAS (35;37;42).

Secondary outcomes, other than those collected specifically for the health economic analysis, will be analysed in a similar manner to the primary outcome as described above. The ASRM and GAD-7 scores will also be examined on a weekly basis as described for the QIDS-SR [33–35]. MADRS, YMRS, SHAPS and QIDS-C between 0 and 12 weeks will be examined in a manner analogous to the primary analysis of the primary outcome [33, 36–38]. Safety and tolerability assessments will include ANCOVA of TSQM and QUIP-RS scores [40, 41], co-varying for baseline score and GAD-7 anxiety scores [35] given the impact of anxiety on tolerability and reported side effects with medication.

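### The covariates named for the TSQM and QUIP-RS ANCOVAs leave out the minimisation factors, at odds with the general rule for secondary outcomes; if omitted, these harm and acceptability tests may be conservative

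*Protocol article*

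**What the plan says.** All statements are in the protocol article.

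- **Allocation** (Randomisation and blinding). The first 10 participants are allocated at random. After that, "a non-deterministic minimisation algorithm is used with an 80% bias in favour of allocations that minimise an imbalance on variables hypothesised to be related to" the expected course of illness. Nine factors are listed: bipolar type, depression severity, age, sex, region, mood stabiliser, antidepressant use, antipsychotic use and number of recent episodes.
- **Primary model** (Statistical analysis). ANCOVA of week-12 QIDS-SR with "adjustment for baseline covariates including initial QIDS-SR score, other minimisation factors and anxiety (GAD-7) score".
- **General rule** (same section). Secondary outcomes, apart from those collected for the health economics, are to be handled much as the primary. MADRS, YMRS, SHAPS and QIDS-C are then sent explicitly to an analogous model.
- **Safety and acceptability scales** (same section). "Safety and tolerability assessments will include ANCOVA of TSQM and QUIP-RS scores", with these models described as "co-varying for baseline score and GAD-7 anxiety scores". The reason given for GAD-7 is that anxiety affects tolerability and reported side effects. The minimisation factors are neither named nor excluded.
- **Status of the two scales.** The abstract counts tolerability and acceptability as secondary outcomes, and both scales stand under Secondary safety and acceptability objectives.
- **Timing** (Table 1). QUIP-RS is collected at week 0. TSQM is first collected at week 6.

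**The concern.** Minimisation makes the arms more alike on the nine factors than chance would. If those factors predict the outcome and the model leaves them out, their variance stays in the residual. The model then reports more uncertainty than the design leaves, and the test rejects less often than its nominal 5%. On an efficacy scale that is a cautious error. On a harm scale it leans towards showing no difference. QUIP-RS is the only scale the article gives for impulse control problems, which it names as a known possible side effect of pramipexole, and TSQM is its scale for side effects and acceptability.

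The specific sentence also comes after the general rule and gives its own reason for GAD-7, which the primary model already contains. An analyst could reasonably take the list as complete and fit a shorter model than the one used for efficacy.

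**Working it through.** **1. The plan's own figures, to fix the numbers analysed.** The article gives no power or standard error for TSQM or QUIP-RS. For QIDS-SR it states that "290 participants provides a 90% power of detecting a 3-point difference in QIDS-SR", with a "standard deviation of 7 and assuming a 20% dropout rate".

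- Week 12: 290 × 0.8 = 232 analysed, 116 per arm. SE = 7 × √(2/116) = 0.919. Power = Φ(3/0.919 − 1.960) = Φ(1.304) = 90.4% (90.2% with the t distribution). This agrees with the stated 90%.
- Week 48, where the article claims "approximately 80% power of detecting a 3.3 point difference in QIDS-SR scores": 290 × 0.5 = 145 analysed, 72.5 per arm. SE = 7 × √(2/72.5) = 1.163. Power = Φ(3.3/1.163 − 1.960) = 81.0% (80.5% with t). This agrees too.

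**2. Extra parameters.** The nine factors have 2, 3, 2, 2, 8, 5, 2, 2 and 2 levels. As categories they need 1 + 2 + 1 + 1 + 7 + 4 + 1 + 1 + 1 = 19 terms.

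**3. Loss from omission, by formula.** Let R² be the share of the variance left after baseline score and GAD-7 that the factors explain. The article gives no value, so 0 to 20% is assumed. Ignoring the cost of the 19 terms, the ratio of standard errors (omitted/included) is 1/√(1 − R²): 1.000, 1.026, 1.054 and 1.118 at R² of 0, 5%, 10% and 20%.

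**4. The same, by simulation.** The stated scheme was simulated: 10 random allocations, then 80%-bias minimisation on nine factors, 290 randomised, 20% dropout, 800 runs per scenario. Factor frequencies and equal contributions of the factors are assumptions. ANCOVA on baseline score and GAD-7 was compared with the same model plus the 19 terms. Power is for a difference of 0.42 residual SD.

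| R² | SE ratio, omitted/included | Power, omitted | Power, included |
|---|---|---|---|
| 0 | 0.98 | 89% | 87% |
| 5% | 1.01 | 88% | 88% |
| 10% | 1.04 | 90% | 91% |
| 20% | 1.10 | 91% | 94% |

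The two methods agree once the cost of the extra terms is counted. That cost is the ratio at R² = 0, which is 0.983: 0.983 × 1.026 = 1.009, 0.983 × 1.054 = 1.036 and 0.983 × 1.118 = 1.099. The break-even is R² = 1 − 0.983² = 3.4%.

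**5. Level of the test.** With 3,000 runs, type I error without the factors was 5.2%, 4.5%, 4.1% and 3.5% at R² of 0, 5%, 10% and 20%, against 4.6% with them. The Monte Carlo error is about √(0.05 × 0.95/3000) = 0.4 percentage points, so the downward trend is clear but the first two values are not distinguishable from 5%. The 800-run results are too noisy to judge the level.

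**6. Week 48.** If the arms were not balanced at all on the factors, the standard error would rise by about √((N − 4)/(N − 4 − 19)). That is √(228/209) = 1.044 at N = 232 and √(141/122) = 1.075 at N = 145. Minimisation brings the first down to about 2%. Dropout weakens the balance, so the week-48 cost lies somewhere between 2% and 7.5%, and the break-even R² between 3.4% and 1 − 122/141 = 13.5%.

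**The case against.** The case against has four parts.

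- **The omission is not established.** The general rule for secondary outcomes arguably covers both scales and carries the minimisation factors with it. The specific sentence does not say that its list is complete, and it says only that the assessments will include these models. This stands. A reader might infer that the harm models certainly omit the factors; the article does not support that. It supports only that two sentences of one section lead to different models.
- **Full detail is left to a statistical analysis plan that is not shown.** True, and silence would be no finding. But the article is not silent: it names covariates, and a plan that followed the sentence literally would inherit the shorter list.
- **The loss is conditional.** The factors are only hypothesised to relate to prognosis, and nothing ties them to impulsivity or satisfaction with medication. At R² of 5% or less there is no material loss, and at 0 the shorter model is slightly better. This stands. The formula's 5.4% and 11.8% at R² of 10% and 20% also overstate the loss, because they ignore the 19 extra terms.
- **A shorter model is defensible later on.** These scales run to week 48, when about 145 participants are expected and some region or mood-stabiliser levels may be thin. This stands as a limit on the gain, not as a reason to leave the wording unsettled.

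Harm is also not judged on QUIP-RS alone, since adverse events and reactions are reviewed for rate, severity, seriousness and causality.

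**Conclusion.** The point holds as an inconsistency with a conditional and modest cost. The sentence on TSQM and QUIP-RS names a shorter covariate list than the primary ANCOVA, while the general rule for secondary outcomes points the other way. If the factors are omitted, the week-12 standard error is about 2% smaller, or 1%, 4% or 10% larger, than in the adjusted model at R² of 0, 5%, 10% or 20%. At 20% the type I error is about 3.5% and simulated power 91% against 94%. These figures rest on assumed values of R², assumed factor frequencies and 20% dropout.

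Two stronger readings should be resisted. Nothing here biases the treatment estimate or inflates the false-positive rate; any error is towards conservatism. Nor does the use of minimisation make allocation predictable: it is central, concealed, non-deterministic and in a double-blind trial.

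Separately, the sentence cannot be applied to TSQM as written. With no TSQM score before week 6, its named covariates reduce to GAD-7 alone.

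**What to change.** Replace the covariate clause with wording such as: ANCOVA of TSQM and QUIP-RS scores will adjust for the same minimisation factors as the primary model, GAD-7 and, where one is collected, the baseline score of the scale. Add two clarifications:

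- TSQM has no baseline score under Table 1, so its model carries none.
- Depression severity is a minimisation factor, and the primary model represents it by the initial QIDS-SR score. State whether these models use that score or the severity category.

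The factors are needed for allocation, so no new data are required. The price is about 19 parameters: about 2% in standard error at week 12 if the factors explain nothing, and somewhat more at week 48 with about 145 participants. A rule set in advance for merging sparse region or mood-stabiliser levels would cover that. If the shorter model is intended, the alternative is to say so and exempt these two scales from the general rule, accepting that the tests may be conservative.

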### Objectives and measures

A key design feature of the PAX-BD study is that outcome measures are mainly collected remotely, mostly using self-report tools implemented on-line using the True Colours platform [32]. Three scales, the Quick Inventory for Depressive Symptomatology – Self Report (QIDS-SR) [33], Altman Self-rating Scale of Mania (ASRM) [34] scale and Generalised Anxiety Disorder-7 (GAD-7) [35] scale are completed on-line by participants weekly from recruitment into the pre-randomisation phase through to the end of follow up. To facilitate comparison of PAX-BD with other studies, the clinician-rated version of the QIDS (QIDS-C) [33], the Montgomery-Asberg Depression Rating Scale (MADRS) [36] and the Young Mania Rating Scale (YMRS) [37] are completed by phone by the study Research Assistants (RAs) at two time points. The timings of the administration of assessments is shown in the Schedule of Events (Table 1).

**Table 1 Tab1:** Schedule of Events

	Screening	Pre-randomisation	Screening and Randomisation	0	Treatment weeks (Post-randomisation)																												Tapering (5, 6, 7)	
					1	2	3	4	5	6	7	8	9 to 11	12	13 to 15	16	17 to 19	20	21 to 23	24	25 to 27	28	29 to 31	32	33 to 35	36	37 to 39	40	41 to 43	44	45 to 47	48	49 to 51	52*
Informed consent (1,2)	✓		✓																															
Demographics	✓	✓																																
Eligibility assessment	✓		✓																															
Randomisation			✓																															
RA safety monitoring call (3, 8)		✓		✓	✓	✓	✓	✓	✓	✓	✓	✓	✓	✓		✓		✓		✓		✓		✓		✓		✓		✓		✓	✓	✓
CSO contact (4)						✓				✓				✓						✓						✓						✓		✓
QIDS-SR, GAD-7 and ASRM		✓		✓	✓	✓	✓	✓	✓	✓	✓	✓	✓	✓	✓	✓	✓	✓	✓	✓	✓	✓	✓	✓	✓	✓	✓	✓	✓	✓	✓	✓	✓	✓
SHAPS				✓						✓				✓																				
WSAS				✓						✓				✓						✓						✓						✓		
TSQM										✓				✓		✓		✓		✓		✓		✓		✓		✓		✓		✓		
QUIP-RS				✓						✓				✓		✓		✓		✓		✓		✓		✓		✓		✓		✓		✓
MADRS, QIDS-C and YMRS				✓										✓																				
IMP Dispensings			✓					✓						✓				✓				✓				✓				✓				
Qualitative Interviews		✓												✓																				
Participant Vouchers														✓												✓								✓
Unblinding (9)																																✓		

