Levels of missing data will be described and baseline values tabulated for those for whom the primary end point can and cannot be calculated in order to summarise any characteristics related to missingness. Data with missing observations due to participant withdrawal or loss to follow-up will be examined to determine both its extent and whether it is missing at random. It is likely that missingness will be related to the outcome itself with depressed participants less likely to complete assessments. However, it has been suggested that even when non-random, a valid approach is to assume randomness since results tend to remain stable when randomness is violated. The primary analysis will utilise complete case analysis with covariate adjustment. This yields similar results to multiple imputation in data that are missing randomly, as long as predictors of missingness are included. If data are missing to a sufficient extent (e.g. between approximately 10 and 20%), the use of appropriate multiple imputation techniques will be considered. The QIDS-SR [33] is assessed weekly. For the primary analysis, the assessment closest to 12 weeks in the range 10–14 weeks will be employed. Missing items from a partially completed TQSM questionnaire [41] will be handled as described in the scoring manual.

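### The complete-case week-12 ANCOVA leaves the earlier weekly QIDS-SR scores of dropouts unused, so the treatment effect is exposed to bias if dropout differs between the arms

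*Protocol article*

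**What the plan says.** All of this is in the protocol article, under Statistical analysis unless noted.

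- **Primary model.** ANCOVA of QIDS-SR at week 12, adjusted for baseline QIDS-SR, the other minimisation factors and baseline GAD-7. Other baseline covariates may be added.
- **One score per person.** "For the primary analysis, the assessment closest to 12 weeks in the range 10–14 weeks will be employed".
- **Who is analysed.** "The primary analysis will utilise complete case analysis with covariate adjustment".
- **Expected missingness.** "It is likely that missingness will be related to the outcome itself with depressed participants less likely to complete assessments".
- **Defence.** The text reports a suggestion that "even when non-random, a valid approach is to assume randomness since results tend to remain stable when randomness is violated". It adds that complete-case analysis resembles multiple imputation for randomly missing data, provided predictors of missingness are included.
- **Multiple imputation.** If enough data are missing (about 10–20% is the example), "the use of appropriate multiple imputation techniques will be considered".
- **Mixed model.** Weekly completion is examined first. "Should this be judged sufficient, a mixed effects linear regression model will be used to account for the repeated measures over time". The Abstract says only that such a model may be used.
- **Available data** (Objectives and measures). QIDS-SR, ASRM and GAD-7 "are completed on-line by participants weekly from recruitment into the pre-randomisation phase through to the end of follow up".
- **Planning figures** (Sample size, power and effect size). 290 randomised, 3-point difference, SD 7, 90% power, 20% dropout at 12 weeks.
- **Comparison.** Health economic analysis commits outright to multiple imputation, reported beside complete cases.

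**The concern.** The defence of complete cases has a condition, and the planned model does not meet it. The predictor of missingness that the plan names is being depressed during the trial. That is measured by the post-baseline weekly scores, and an ANCOVA with baseline covariates cannot include them. The two analyses that could use those scores are not committed: imputation is left for consideration, and the mixed model depends on completion being good enough, with no threshold. The model is therefore set aside when completion is poor, which is when it is most needed.

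The estimate at stake is the single confirmatory one. The arms could plausibly lose people for different reasons. Under Intervention, dosing is titrated to the maximum tolerated dose. The safety objectives name mania, psychosis and impulse control disorders as possible effects of the drug. If placebo participants leave because they remain depressed and pramipexole participants leave for reasons unrelated to mood, the placebo completers look too well and the benefit is understated. The opposite pattern overstates it.

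**Working it through.** **1. The plan's own figure.** Inputs: difference 3, SD 7, two-sided 0.05, power 90%, dropout 20%.

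n per arm = 2(1.960 + 1.282)² × 7² / 3² = 114.4, so 115 per arm and 230 in total. 230 / 0.8 = 287.5, so 288, against 290 stated. With 290 × 0.8 = 232 analysed (116 per arm), t-test power is 90.2%. The sample size reproduces and is not in question.

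**2. People lost to the primary analysis.** 290 × 0.20 = 58.

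**3. When complete cases mislead.** Let p be the dropout proportion in an arm and d the mean week-12 score of its dropouts minus that of its completers. For unadjusted means (pramipexole minus placebo):

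true effect − complete-case effect = p_pram × d_pram − p_plac × d_plac

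The values of d are assumptions:

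- 20% in each arm, d = 4 in both: 0.8 − 0.8 = 0.
- 25% pramipexole, 15% placebo, d = 4 in both: 1.0 − 0.6 = 0.4.
- 20% in each arm, d = 4 in one arm only: 0.8, with the sign depending on the arm.

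Outcome-related dropout alone does not bias the difference. A difference between arms in rate or mechanism does.

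**4. Simulation.** Assumptions not in the documents: 200,000 participants; weekly scores for weeks 0–12; SD 7; random intercept plus AR(1) errors with correlation 0.8 or 0.95; true benefit about 3; 20% dropout per arm. The weekly log-odds of dropout rise by s per 7 QIDS-SR points, with s = 1 where dropout is symptom-driven and 0 where it is not, unless stated. Monte Carlo error is about 0.03. Ranges cover the two correlations.

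| Dropout depends on | True benefit | Complete-case ANCOVA | Likelihood-type analysis, all weekly scores |
|---|---|---|---|
| Last seen score, alike in both arms | 2.98 | 2.96–2.98 | 2.97–2.98 |
| Last seen score, half as strong on pramipexole (s = 0.5) | 3.01–3.02 | 2.79–2.87 | 3.00–3.01 |
| Last seen score, placebo only | 2.98–3.04 | 2.60–2.75 | 2.99–3.01 |
| Last seen score, pramipexole only | 3.00–3.03 | 3.27–3.39 | 2.99–3.03 |
| Last seen score, opposite directions (pramipexole 1, placebo −0.5) | 3.00 | 3.45–3.64 | 2.99 |
| Unseen current score, placebo only | 2.96–3.02 | 2.45–2.72 | 2.79–2.95 |
| Unseen current score, opposite directions | 2.95–2.97 | 3.52–3.76 | 3.06–3.23 |

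Across the patterns that differ between arms, the bias runs from 3.02 − 2.87 = 0.15 to 3.76 − 2.97 = 0.79 points. That is 5% to 26% of the 3-point target.

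A second simulation (145 per arm, two-weekly visits, SD about 6.5, 3,000 trials per pattern) gave complete-case benefits of 2.94 with dropout alike in both arms, 2.44 with symptom-driven dropout on placebo only, and 2.20 when that dropout followed the unseen score. The repeated-measures estimates were 2.99, 3.00 and 2.66.

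**5. Power if the effect is understated** (t-test, SD 7, 116 per arm; standard error 7√(2/116) = 0.919):

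| Expected estimate | Power |
|---|---|
| 3.00 | 90% |
| 2.94 | 89% |
| 2.75 | 85% |
| 2.60 | 80% |
| 2.44 | 75% |

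**The case against.** - **The plan names no difference between arms.** It says depressed participants will be missed more often, without distinction by arm. Under that mechanism acting alike, the complete-case estimate is 2.94–2.98 against 3. This stands: material bias needs a further assumption that the documents do not make.
- **Parts of the plan reduce the problem.** Under Recruitment, those who stop medication and consent are followed to 48 weeks, so stopping for side effects need not mean a missing score. The 10–14 week window gives up to five weekly chances. Missingness will be described and baseline values tabulated by endpoint availability. At 20% missing, imputation would be considered, and it could use the weekly scores. These points stand as mitigation. None helps a person who withdraws or stops rating, and none is a commitment to use the earlier scores.
- **Power.** A reader might infer that the trial's power falls from 90% to 75%. The documents do not support that. It is one end of a range, computed for an unadjusted t-test, whereas the planned analysis is baseline-adjusted. In the second simulation the complete-case ANCOVA kept 86% power at the 2.44 estimate, against 97% for the repeated-measures model. Reaching 2.44 needs, for example, placebo dropouts 0.56 / 0.20 = 2.8 points worse than placebo completers with no such gap on pramipexole.
- **Timing.** A reader might also infer that nearly all dropouts leave several scores behind, or that the completion check is made with outcomes by arm in view. The text gives neither the timing of dropout nor the blinding of that check.
- **The mixed model is no complete cure.** It assumes data missing at random. This stands: in the tables above it reduces bias from unseen scores but does not remove it.

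**Conclusion.** The point holds as a weakness that should be fixed, not as proof that the primary result will be biased. The article fixes a primary analysis that leaves out about 58 of 290 participants and any weekly scores they gave before week 10, and it defends this by a condition the model cannot meet for the predictor it names. The stronger reading, that expecting sicker participants to go missing makes the treatment difference biased, is not supported: with the same mechanism in both arms the bias is at most about 0.06 points.

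If mechanism or rate differs between arms, the bias is roughly 0.15–0.8 points, and its direction cannot be known in advance. These sizes rest on assumed dropout strengths, correlations and dropout–completer gaps. The conclusion concerns what the article fixes, not detail left to the SAP.

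**What to change.** Make the primary estimate the week-12 contrast from a repeated-measures model on all weekly QIDS-SR scores from weeks 1–12 in all randomised participants. Include treatment-by-week, baseline QIDS-SR-by-week, the minimisation factors and baseline GAD-7. Fit it whatever the completion rate, with a fallback covariance structure named in advance in case the 12-visit model does not converge. A commitment to multiple imputation that uses the weekly scores would serve equally well.

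Keep the complete-case ANCOVA on the 10–14 week score as a sensitivity analysis. Add a delta-adjusted not-at-random analysis in which the assumed shift for missing scores can differ by arm, because the repeated-measures model does not cover dropout driven by unseen scores.

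The cost is wording in the protocol and SAP, agreed before unblinding. No new data are needed. The 12-visit weekly model with all covariates was not itself simulated here, which is a further reason to name the fallback.

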Multiple imputation will be used to deal with missing data. Results from both the full imputed dataset and from the complete case analysis will be compared and reported as means with standard deviations or as mean differences with 95% confidence intervals. Differences in mean costs and effects will be compared in a regression framework with a *p*-value less than 5% considered as statistically significant. Non-parametric bootstrapping [64] from the cost and effectiveness data will be used to generate a joint distribution of the mean incremental costs and effects for the options under comparison and to calculate the 95% confidence intervals of the ICERs. Uncertainty around the main cost-effectiveness estimates will be represented by cost-effectiveness acceptability curves (CEACs) using the net benefit approach [65, 66]. CEACs show the probability that each option is cost-effective to a range of maximum values (ceiling ratio) that a decision maker might be willing to pay for an additional unit of improvement in outcomes.

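### For the clinical 48-week secondary outcomes the only method fixed is, on a natural reading, baseline-adjusted complete case, although the plan expects to lose half the participants and the more depressed ones first

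*Protocol article*

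**What the plan says.** **Expected loss.** The section on sample size, power and effect size takes its rates from an earlier UK trial in bipolar depression: "Dropout rates in this study were 20% at 12 weeks and 50% at 52 weeks". It applies the 20% to week 12 and the 50% to week 48.

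**Expected mechanism.** The Statistical analysis section says that missingness probably depends on the outcome, with depressed participants completing fewer assessments. It then accepts treating the data as missing at random.

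**Method.** The same section sets complete case with covariate adjustment for the primary analysis. It defends this as close to multiple imputation provided that predictors of missingness are in the model. On imputation itself: "If data are missing to a sufficient extent (e.g. between approximately 10 and 20%), the use of appropriate multiple imputation techniques will be considered".

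**Secondary outcomes.** These include remission and response at 12 and 48 weeks, proportion of time over 48 weeks free of depressive or manic symptoms, and WSAS. Apart from the health economic outcomes, they "will be analysed in a similar manner to the primary outcome as described above". No separate missing-data rule is given for week 48.

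**Two exceptions.** A mixed model will be used for weekly QIDS-SR if completion is judged adequate, and ASRM and GAD-7 are treated likewise. The Health economic analysis section states: "Multiple imputation will be used to deal with missing data". It reports imputed and complete-case results together.

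**The concern.** The article foresees heavy loss related to outcome and leaves the 48-week clinical endpoints with the method most exposed to it. Its own defence of complete case needs the predictors of missingness in the model, but the ANCOVA adjusts for baseline covariates only. If participants leave because they worsen after randomisation, the predictors are the post-baseline weekly scores, which that model omits. The gap matters more over 48 weeks than over 12.

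The mixed model would use those scores, but it depends on adequate weekly completion, and heavy dropout is what could switch it off. It is described only for the weekly scales. It does not by itself deliver remission, response, WSAS or time free of symptoms.

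The imputation sentence does not close the gap. Its example range already has the expected week-12 loss at its upper end, it is silent on anything higher, and imputation is only to be considered.

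At stake are the long-term remission and response rates that clinicians would quote, and the size of the 48-week treatment difference.

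**Working it through.** **1. The plan's own figures.** Inputs: "A two-sided significance level of *p* < 0.05 will be used throughout"; 1:1 allocation (Intervention section); "290 participants provides a 90% power of detecting a 3-point difference in QIDS-SR"; "standard deviation of 7 and assuming a 20% dropout rate as seen in the CEQUEL study"; and for week 48 "This sample size also provides approximately 80% power of detecting a 3.3 point difference in QIDS-SR scores" with 50% dropout.

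- Week 12: n per arm = 2(1.960 + 1.282)² × 7²/3², rounded up to 115. The total is 230, and 230/(1 − 0.20) = 287.5, or 288 against 290 stated. With 145 × 0.8 = 116 per arm, power is 90.4% (normal) or 90.2% (t).
- Week 48: 145 × 0.5 = 72.5 per arm. SE = 7 × √(2/72.5) = 1.163, and 3.3/1.163 = 2.84. Power = Φ(2.84 − 1.96) = 81.0% (normal) or 80.5% (t), against about 80% stated.

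Both figures reproduce. The 48-week power therefore counts only the 145 expected completers.

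**2. Expected loss against the example band.**

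| Missing | Participants of 290 |
|---|---|
| 10% | 29 |
| 20% (expected, week 12) | 58 |
| 50% (expected, week 48) | 145 |

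The expected week-48 loss is 145/58 = 2.5 times the upper end of the band.

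**3. How bias grows with missingness.** In one arm with missing fraction f, completer mean − full mean = f × (completer mean − dropout mean). The bias in the unadjusted treatment difference is therefore f × (difference between arms in that gap). The documents give no figure for the gap difference, so a range of 1 to 3 QIDS-SR points is assumed.

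| f | Bias in the difference (points) |
|---|---|
| 0.10 | 0.1 to 0.3 |
| 0.20 | 0.2 to 0.6 |
| 0.50 | 0.5 to 1.5 |

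The last row compares with a 3.3-point target. If the gap is the same in both arms the difference is unbiased, but each arm's own mean is not.

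**4. Simulation of the method as written.** 145 per arm, SD 7, true week-48 difference 3.3, 50% lost per arm, complete case adjusted for baseline. Assumption: where dropout is informative, it follows the last observed score.

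| Dropout follows last score in | Adjusted complete-case difference | Error against 3.3 |
|---|---|---|
| both arms | about 3.2 | −0.1 |
| placebo only | 2.1 to 2.7 | −1.2 to −0.6 |
| pramipexole only | about 4.4 | +1.1 |

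Completer remission was about 17% on placebo and 32% on pramipexole, against a truth of 11% and 23%. A separate simulation with score-driven dropout in both arms gave 20% and 37% against 13% and 25%.

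**5. Sensitivity to the set-up.** A further check used within-person correlation 0.5 to 0.7 and a dropout log-odds slope of 1 per SD. With dependence on placebo only, it gave adjusted differences of 2.35 and 2.52, where the unadjusted ones were 1.34 and 0.63. With dependence on pramipexole only, the adjusted values were 4.1 to 4.2. With the same slope in both arms the result was about 3.3. Direction and rough size agree with step 4. Baseline adjustment removes much of the bias but not all of it.

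**The case against.** Several points on the other side stand.

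- **The complete-case sentence names only the primary analysis.** It also comes after the sentence on secondary outcomes, whose reference back reaches the ANCOVA and the conditional mixed model. That the 48-week outcomes follow complete case is an inference. It is the natural one, since no other rule is offered. For time free of symptoms, complete case is not even defined.
- **The band is an example, and approximate.** A reader might infer that 50% lies above a ceiling at which imputation stops. The text does not say so. It can equally be read as a level from which imputation is considered, which 50% would meet. Either way, nothing is committed.
- **Not every 48-week outcome is exposed.** The economic outcomes are imputed, and the weekly scales may get a mixed model. Nor do the clinical and economic results simply rest on different populations, because the economic section also reports complete case.
- **The treatment difference need not be badly wrong.** A reader might infer that the 48-week effect could nearly vanish. Values near or below 1 point arise only without baseline adjustment and with outcome-driven dropout confined to placebo. The plan specifies adjustment, and the bias can also go upward.
- **The 50% is a planning figure.** Those who stop medication can, with consent, be followed to 48 weeks, so the loss may be smaller.
- **Full analysis details are deferred to an SAP that is not shown.** It may settle the matter, but the article's own text should not point the other way.

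**Conclusion.** The point holds for the non-economic 48-week secondary outcomes: remission, response, WSAS, proportion of time free of symptoms, and QIDS-SR if the conditional mixed model is not used. For these the article fixes, on a natural reading, only baseline-adjusted complete case, while planning for 50% loss that it expects to depend on depression.

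The firmest consequence is remission rates that are too high in both arms, by roughly 6 points on placebo (17 − 11) and 9 on pramipexole (32 − 23) in the simulation. The adjusted mean difference is nearly right if the dropout mechanism is the same in both arms, and lies between about 2.1 and 4.4 against 3.3 if it differs. These sizes rest on an assumed mechanism. The documents give no data on it, so they are illustrations and not forecasts.

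The week-12 primary endpoint and the reproduced power figures are not in question here. Severity: should-fix.

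**What to change.** 1. Remove the 10 to 20% example band, so that the method does not depend on the observed level of missingness.
2. For continuous weekly outcomes to week 48, use the mixed model on all weekly scores, without the condition that completion first be judged adequate.
3. For remission, response, WSAS and proportion-of-time outcomes at 48 weeks, use multiple imputation with observed post-baseline scores in the imputation model, and baseline covariates and arm as well.
4. Keep baseline-adjusted complete case as a sensitivity analysis.
5. Add a sensitivity analysis for missingness that depends on the unobserved outcome. Steps 2 and 3 assume missing at random given the observed scores, and the article itself doubts randomness.

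The cost is revised wording and modest extra programming. The weekly scores are already collected, so there is no added burden on participants. Nothing in the article says that the economic imputation will cover weekly QIDS-SR, so the clinical imputation should be budgeted as separate work, although the two models are best kept consistent.
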